### Risk of Harm

All equipment used in the study meets the requirements for patient safety and has previously been used in research projects. Participants will have blood samples taken before visits (maximum 18 mL). The total amount of blood collected during the entire study period is at the same level as during the standard course of treatment and is considered safe.

Participants will not have any study-specific clinical measurements taken besides three 2-week periods of CGM measurement. During the sensor placement, participants may experience minor and brief discomfort. The sensor is generally well-tolerated, and only a few potential discomforts are associated with its use. Some participants may experience mild skin irritation or redness where the sensor is inserted. There may be a slight discomfort during the insertion process, although it is generally brief. In rare cases, an allergic reaction to the sensor adhesive or materials may occur, leading to more significant skin irritation. It is also worth noting that the sensor needs to be replaced twice, which involves removing the old sensor and applying a new one, which can cause minor discomfort. However, these discomforts are small and temporary. A rare complication is a superficial skin infection obtained in connection with penetration of the skin. The risk of superficial phlebitis is minimized by following hygiene standards, including double cleansing of the skin with an alcohol swab and using sterile materials. Superficial phlebitis is not dangerous. Medication will be reviewed and adjusted according to current clinical guidelines. Participants can contact the physician and diabetes nurse or use the hotline at SDCC about medical issues, for example, concerns related to medication use.

### Dissemination

Appointed researchers affiliated with SDCC will be granted access to data. The principal investigator will facilitate direct access to source data and documents for regulatory inspection. Since we anticipate no adverse effects associated with the intervention, recording of harm or side effects will be conducted. Positive and negative study results and inconclusive findings will be presented at conferences and published in international peer-reviewed journals. All coauthors are expected to adhere to the guidelines of the International Committee of Medical Journal Editors, and no professional writers will be involved in the writing process.

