### Study Visits

The visits will be run by the same diabetes nurse and endocrinologist under the responsibility of the investigator. Visits with dieticians will be arranged if requested by participants (up to 60 min per visit). For logistical reasons, windows are allowed for the visits (±30 days). The intervention staff includes the same diabetes nurse and endocrinologist, each overseeing the 48 participants in the intervention group. The 48 control participants will continue their care with their usual HCPs. A detailed visit flow is presented in Figure 2.

#### Visit 1

The first visit, lasting 60 minutes, will involve meeting with a diabetes nurse. During this visit, the focus will be on introducing the participant to the course of treatment and to a continuous glucose monitor (CGM; FreeStyle Libre 2 sensor), which the participant will use for the following 2 weeks. This will enable the participant to gain insight into personal glucose levels. In addition, the nurse will provide information about T2D and its treatment and discuss everyday challenges and topics relevant to the participant.

#### Visit 2

The second visit, lasting 60 minutes, will involve the same diabetes nurse. The main aim is to talk about pattern identification obtained from the CGM sensor for the past 2 weeks to enhance knowledge of lifestyle factors contributing to stable or fluctuating glucose levels. The nurse will engage in a dialogue about the challenges participants face in everyday life. A new sensor will be applied to the participant for the upcoming 2-week period.

#### Visit 3

During the third visit, lasting 45 minutes, the participant will meet with an endocrinologist. Patterns derived from the CGM sensor will be discussed to enhance participants’ comprehension of unique glucose levels and determine if any changes or solutions discussed during the second visit have been implemented and proven effective in promoting more stable glucose levels. The endocrinologist will evaluate patterns of variation, for example, focus on hypoglycemia, and make necessary adjustments in pharmacological treatment. The treatment plan will be negotiated with the participant, providing information on the rationale for the change in treatment regimen and potential benefits and risks. The participant will also be guided to continue self-monitoring of blood glucose according to individual plans.

#### Visit 4

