During the fourth visit (2x30 mins), the participant will meet with the same endocrinologist and diabetes nurse. The main purpose is to evaluate and follow up on the participant’s everyday life with diabetes, medication use, and individual needs. The aim is to support the participant’s positive experience with the treatment and lifestyle changes, address misperceptions, and reinforce the information provided. If necessary, the endocrinologist will adjust the medication regimen.

#### Visit 5

During the fifth visit, lasting 30 minutes, the participant will meet with the same endocrinologist. The main purpose is to evaluate and follow up on the participant’s medication usage and individual needs. The aim is again to support the participant’s positive experience with the treatment and lifestyle changes, address misperceptions, and reinforce the information provided. If necessary, the endocrinologist will adjust the medication regimen.

#### Visit 6

During the sixth visit (20+30 min), the participant will again meet the same endocrinologist and diabetes nurse. The primary aim is to provide a comprehensive overview of the treatment progress and patterns obtained from the CGM sensor for the past 2 weeks. The participant will be instructed to apply the sensor at home 2 weeks before the last visit. If the participant prefers, they can be booked for a short visit at SDCC with the diabetes nurse to apply the sensor. The last visit will serve as an opportunity to ask any questions, clarify doubts, or express any specific needs the participants may have.

Besides the 6 visits, the participant will receive links to 4 short videos about T2D developed by the Danish Diabetes Knowledge Center at SDCC. The videos are translated into Urdu, Arabic, or Turkish and include knowledge on (1) T2D, (2) complications associated with T2D, (3) exercise and diabetes, and (4) carbohydrates and diabetes (for details on content, refer to [37]). Participants in the intervention group may also have visits, for example with a psychologist and a podiatrist, as part of their usual course of treatment.

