#### Secondary Outcomes

The secondary exploratory outcomes encompass a range of metabolic and behavioral factors that may be linked to the intervention. These involve changes from baseline to the end of the intervention (1 year), including plasma lipids, markers of kidney function, hormones involved in glucose metabolism, blood pressure, resting heart rate, CGM (time-in-range, time-above-range, and time-below-range), body weight, and use of diabetes medication (Table 1).

**Table 1 table1:** Data collection.

Visit sequence number			Visit 1		Visit 2		Visit 3		Visit 4		Visit 5		Visit 6

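### The harms sentence contradicts itself and the risk section, and the only hypoglycemia-related outcome shown exists in the intervention arm alone

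*Protocol article*

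**What the plan says.** The statement on harms stands in the Dissemination section of the protocol article: "Since we anticipate no adverse effects associated with the intervention, recording of harm or side effects will be conducted".

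The Risk of Harm section describes effects of the glucose sensor, from brief discomfort and mild irritation upward: "In rare cases, an allergic reaction to the sensor adhesive or materials may occur, leading to more significant skin irritation". It adds: "A rare complication is a superficial skin infection obtained in connection with penetration of the skin". On drugs it says: "Medication will be reviewed and adjusted according to current clinical guidelines".

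Under Study Visits, visit 3 reads: "The endocrinologist will evaluate patterns of variation, for example, focus on hypoglycemia, and make necessary adjustments in pharmacological treatment". Visits 4 and 5 each repeat: "If necessary, the endocrinologist will adjust the medication regimen".

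Secondary Outcomes lists change in CGM time-in-range, time-above-range and time-below-range. Table 1 ticks CGM at visits 2, 3 and 6 and has no row named for adverse events or hypoglycemic episodes. The paragraph on contamination that closes Study Visits says that controls get none of the materials or technology given to the intervention group.

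**The concern.** Two things look wrong. First, the sentence's conclusion does not follow from its premise. Either a negative has been dropped and harms are not recorded, or they are recorded and the reason given is misplaced. These are opposite plans, and the sentence does not say which one applies.

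Second, the premise is not neutral. The intervention aims to lower HbA1c, in part by reviewing and changing medication, and hypoglycemia is the foreseeable harm that the article itself names. If the trial meets its superiority criterion (a difference of at least 5 mmol/mol with P<.05), readers deciding on implementation will ask whether hypoglycemia differed between the arms. That question needs the same information from both arms, and the one relevant outcome shown appears to be collected in one arm only.

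**Working it through.** The article gives no figure on harms to reproduce, so the main check sets its statements side by side.

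1. **Premise against conclusion (Dissemination).** Premise: no adverse effects are anticipated. Conclusion: harms will be recorded. Joined by a causal word, the premise argues for the opposite of the conclusion. This is a defect in what is stated, not a detail left out.

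2. **Premise against Risk of Harm.** That section anticipates discomfort, skin irritation, allergic reaction and superficial skin infection from a sensor that belongs to the intervention. Rare and mild effects are still adverse effects, so the two sections conflict directly.

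3. **Premise against Study Visits.** Visit 3 looks for hypoglycemia in the CGM data and allows drug changes; visits 4 and 5 allow further changes. This does not say that the intervention causes hypoglycemia. It does show that the authors regard hypoglycemia as relevant to these patients and that drug treatment may change, which is hard to square with expecting no adverse effects. It is a tension, weaker than the conflict in step 2.

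4. **Who has a hypoglycemia-related outcome.**

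| | Intervention (48) | Control (48) |
|---|---|---|
| CGM time-below-range | scheduled: visits 2, 3 and 6 | technology withheld |
| Row in Table 1 named for hypoglycemic episodes or adverse events | none | none |

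Time-below-range is defined as an outcome, but as written it has no control value. A change from baseline can be described within the intervention arm; a between-arm difference cannot be estimated.

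5. **What a record-based comparison could show.** The article gives no rate of severe hypoglycemia. Assume, for illustration only, a yearly risk p between 1% and 5% per participant.
   - Expected participants with an event per arm: 48 × 0.01 = 0.48 to 48 × 0.05 = 2.4.
   - Chance that an arm of 48 shows none: (1 − p)^48, which is 0.99^48 = 0.62 at 1% and 0.95^48 = 0.085 at 5%.
   - If none of 48 has an event, the one-sided 95% upper limit for the risk is 1 − 0.05^(1/48) = 0.061, about 6%.

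Such counts are worth reporting but cannot support a formal test or a claim of equal safety.

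**The case against.** The best defense is that the sentence, read literally, does promise that harms will be recorded. How they are collected (form, timing, chart review, both arms) is what a condensed article leaves to the full protocol, which is not shown. That stands: the lack of an adverse-event row in Table 1 is no finding by itself, and nothing in the article says that recording will differ by arm. It does not rescue the sentence, which is wrong as printed, nor the conflict with Risk of Harm.

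It can also be said that looking for hypoglycemia at visit 3 is a safeguard, and that drug changes follow current guidelines. That is fair, and it is why the sensor effects carry the direct contradiction here.

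A third reply is that the CGM and risk paragraphs speak of participants without naming an arm, so controls might wear sensors for measurement only. The contamination paragraph, as written, excludes this. If it is not what the authors intend, the two places need reconciling.

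Some stronger readings are tempting, and the article does not support them:

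- **No harm is scheduled in either arm.** Time-below-range is scheduled in the intervention arm.
- **Benefit cannot be weighed against harm at all.** The gap is a like-for-like comparison of hypoglycemia in the schedule shown. Other information may be collected under the full protocol.
- **None of the 48 controls has any harm measure.** Table 1 includes a diabetes patient-reported outcome questionnaire whose items are not given, so it cannot be said that hypoglycemia is not asked about.
- **Spontaneous reporting is inflated in proportion to visits (6 against 3 to 4 a year).** Controls may also have podiatry, eye screening and other contacts, a hotline is available, and the first intervention visits are close together. Visit counts are not a sound measure of the opportunity to report.

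**Conclusion.** The point holds as an internal contradiction on a safety matter with one consequence for design. The harms sentence contradicts itself. Its premise conflicts with the sensor effects in Risk of Harm and fits poorly with the medication changes and hypoglycemia focus in visits 3 to 5. From the schedule shown, hypoglycemia cannot be compared like for like between the arms, because time-below-range is available for the 48 intervention participants and not for the 48 controls.

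This rests on two assumptions: that the contamination paragraph means what it says about technology, and that no other hypoglycemia outcome lies in documents not shown. The contradiction in the sentence depends on neither. The primary HbA1c analysis and the sample size are untouched; what suffers is the interpretation of a positive result.

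**What to change.** - **Text.** Remove the premise that no adverse effects are anticipated. State plainly that harms are recorded in both arms by the same method, and bring the sentence into line with Risk of Harm and Study Visits.
- **Data.** For all 96 participants, extract severe hypoglycemia and diabetes-related emergency contacts or admissions over the year from the clinic record, using one definition and one time window in both arms. All participants are patients of the same outpatient clinic, so this remains possible although enrollment is complete.
- **Reporting.** Give counts by arm descriptively, without a test. Report time-below-range as a within-intervention-arm measure only, and say so where the secondary outcomes are listed.

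A recall question should not be the main source. Added now, it would miss anyone who has already had the last visit, and it would need translation into three languages.

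The cost is a small chart-extraction burden and possibly an ethics notification. Few events are likely at 48 per arm, so the result will be imprecise. The change concerns recording and reporting only and alters no clinical care.

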### Ethics Approval

The study has been approved by the Ethics Committee of the Capital Region of Denmark (H-23042245) and the Research Legal Affairs of the Capital Region of Denmark (P-2023-14503). The study will be conducted following the Declaration of Helsinki and will comply with the Danish Data Protection Agency and the General Data Protection Regulation. Adequate blinding of all personal data during data processing and publication will be ensured. The participants are covered by the Patient Compensation Association according to the Danish Act on the Right to Complain and Receive Compensation within the Health Service.

## Results

Study funded in June 2023. By March 2025, all participants were successfully enrolled in the study. Data collection will proceed until December 2025, allowing for comprehensive data gathering. Once data are collected, the research team will begin the analysis process, with the first results anticipated to be available by March 2026.

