**Results:**

A 5.0-mmol/mol change in HbA_1c_ is the minimally important difference, requiring 88 participants. To allow for uncertainties and dropouts, the total was increased to 96. As of January 2025, a total of 88 participants have been recruited. Recruitment was completed in March 2025. Data collection will continue until December 2025, with the first results expected by March 2026.

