### Recruitment, Screening, and Consent

We plan to recruit 96 Arabic-, Turkish-, or Urdu-speaking individuals with T2D from the outpatient T2D clinic at SDCC. During the latest visit to the usual course of treatment at SDCC, potential participants will receive a brief introduction to the person-centered and culturally sensitive course of treatment in the type 2 diabetes (ACCT2) study. If interested, potential participants will be met by a project worker who will provide an oral introduction and, if interested, play an audio recording containing study information in Urdu, Arabic, or Turkish, depending on the participant’s preference. All study participants will receive written study information in their native language. The information will be given in quiet surroundings at SDCC. The ability to bring one companion is allowed.

The project worker will have a written informed consent ready to sign and be available to address any questions. Participants may have at least 24 hours to consider participation. A participant folder containing the written study information and the written informed consent will be handed to the potential participant, and a project worker will follow up with a phone call within a week. If the participant wishes to take part in the study, the written informed consent must be signed and forwarded to the project worker. By January 16, 2025, a total of 88 out of 96 participants were recruited. The recruitment process will continue until March 2025.

To ensure accessibility, all written information is translated into Urdu, Arabic, or Turkish by international standards [30]. Study participants are informed that they can always withdraw their commitment to participate. The individual participant’s right not to know their data will be respected.

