### Outcomes

#### Primary Outcome

The primary outcome is changes in HbA_1c_ (mmol/mol) from baseline to the end of the 1-year intervention.

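### Data collection is stated to end in December 2025, which is too early for the 1-year primary outcome of participants enrolled up to March 2025

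*Protocol article*

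**What the plan says.** All statements are in the protocol article.

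- **End of enrolment.** The Abstract (Results) says "Recruitment was completed in March 2025". The main Results section says "By March 2025, all participants were successfully enrolled in the study. Data collection will proceed until December 2025". Recruitment, Screening, and Consent, written earlier, says "The recruitment process will continue until March 2025".
- **Progress in January.** The same recruitment section reports "By January 16, 2025, a total of 88 out of 96 participants were recruited", so 8 were still to come.
- **Primary outcome.** It is defined as "changes in HbA_1c_ (mmol/mol) from baseline to the end of the 1-year intervention". The Abstract (Methods) places assessments at baseline and 1 year.
- **Visit window.** Under Study Visits, "windows are allowed for the visits (±30 days".
- **Order of events.** Under Randomization, allocation follows written consent and precedes the first visit, so visit 1 cannot come before enrolment.
- **End of data collection.** The Abstract says "Data collection will continue until December 2025, with the first results expected by March 2026". The main Results section repeats both dates and puts the start of analysis after the data are in.
- **Analysis trigger.** Statistical Analysis calls for an intention-to-treat analysis of everyone randomized, run once the last participant has had the final visit.

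**The concern.** From the end of enrolment (March 2025) to the end of data collection (December 2025) is 9 to 10 months, but the primary outcome needs 12, or 11 with the full early window. If the December date were followed, participants enrolled late would have a primary outcome that is either missing or measured before the window opens. Visit 6 is also the closing visit of the intervention, with sensor data from the two preceding weeks, so an early close would shorten the treatment course as well as the follow-up.

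The December date also conflicts with the analysis trigger. An analysis of all randomized participants after the last final visit cannot rest on data collection that stops before that visit is due. Loss of this kind would be avoidable and would come on top of any real dropout.

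**Working it through.** **Inputs**

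- Scheduled 1-year visit: visit 1 + 365 days (Abstract, Methods; Primary Outcome).
- Earliest in-window visit: visit 1 + 365 − 30 = day 335. Latest: visit 1 + 365 + 30 = day 395 (Study Visits).
- End of data collection: 31 December 2025, the most lenient reading of December 2025.
- Last enrolment: 1 to 31 March 2025. As a lenient variant, 28 February 2025, if *by March* is taken to mean before March.
- Assumption: visit 1 falls on the day of enrolment. A later visit 1 only makes the gap larger.

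**Step 1. Latest visit 1 compatible with the stated end date**

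- Without the window: 31 Dec 2025 − 365 days = 31 Dec 2024.
- With the full early window: 31 Dec 2025 − 335 days = 30 Jan 2025.
- With the full early window, if data collection ended on 1 December: 1 Dec 2025 − 335 days = 31 Dec 2024.

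**Step 2. Follow-up available by 31 December 2025**

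| Visit 1 | Days to 31 Dec 2025 | Against day 335 | Earliest in-window visit 6 | Nominal visit 6 | Latest in-window visit 6 |
|---|---|---|---|---|---|
| 16 Jan 2025 | 349 | 14 to spare | 17 Dec 2025 | 16 Jan 2026 | 15 Feb 2026 |
| 28 Feb 2025 | 306 | 29 short | 29 Jan 2026 | 28 Feb 2026 | 30 Mar 2026 |
| 1 Mar 2025 | 305 | 30 short | 30 Jan 2026 | 1 Mar 2026 | 31 Mar 2026 |
| 31 Mar 2025 | 275 | 60 short | 1 Mar 2026 | 31 Mar 2026 | 30 Apr 2026 |

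The stated December 2025 end therefore cannot be reproduced from the article's own enrolment, follow-up and window figures. Even the combination of a 28 February enrolment, a 31 December end and the full early window falls 29 days short.

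**Step 3. How many are affected**

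- Recruited after 16 January 2025: 96 − 88 = 8, or 8/96 = 8.3%.
- Of these, anyone with visit 1 between 17 and 30 January still fits, with 348 to 335 days, but only by using the early window. The article gives no enrolment dates within this group.
- Some of the first 88 may also have had visit 1 after 30 January, because consent and randomization come before it.
- So 8 is neither established nor a ceiling. What follows from the dates is at least one, the last-enrolled participant.

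**Step 4. The results date**

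For a participant starting in March 2025, the nominal visit 6 falls in March 2026, the month by which first results are promised. For a 31 March start, the window runs to 30 April 2026, after that date.

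**The case against.** The strongest reply is that the December date is a forecast in the status reporting of a journal article, while the rules that govern the trial are sound. The outcome is fixed at one year, and the analysis waits for the last participant's final visit. No section closes a participant out early or provides for administrative censoring. If those rules are followed, the date slips and no endpoint is lost.

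Part of this stands. The article does not show that anyone decided to truncate follow-up, so the point is an inconsistency and not a design choice. But the analysis trigger does not cure the conflict. The end date is given twice, without qualification and after recruitment had closed, and nothing says which statement prevails. Nor is this a matter of detail left to a fuller protocol, because the article itself states dates that are incompatible.

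A reader might infer more in two ways:

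- **That 8 of 96 will lose the primary outcome, using up the whole margin above the 88 required.** The documents do not support this. Starts up to 30 January are in window, later enrolment dates are not given, and late participants might be measured early and not lost.
- **That the trial loses a definite amount of power.** Any such figure needs an assumed number lost, an assumed split between arms and a choice of model. The article does not fix the first two, and the inconsistency does not depend on them.

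**Conclusion.** The stated end of data collection is wrong as written. It cannot be reconciled with enrolment completed in March 2025, a 1-year primary outcome with a 30-day window, and an intention-to-treat analysis after the last final visit. Any participant with visit 1 after 30 January 2025 cannot have an in-window visit 6 by 31 December 2025, and the shortfall for March starts is 30 to 60 days. The number of participants affected is at least one and otherwise unknown.

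This rests on three assumptions: completion of recruitment in March means that the last participant entered then (or at the end of February on the lenient reading); visit 1 is not before enrolment, as the Randomization section implies; and the 30-day window applies to the 1-year assessment in both arms. The visit-flow figure is not available, so the scheduled day of visit 6 is taken from the text.

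**What to change.** Reconcile the dates in the Abstract and the Results section. Define the end of data collection by the last participant: last visit 1 + 1 year, plus up to 30 days. For a last visit 1 on 31 March 2025 this is as late as 30 April 2026; for 1 March 2025 it is 31 March 2026. Move the start of analysis and the first-results date, now March 2026, behind that point. State that no participant is closed out before an in-window visit 6.

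The cost is a delay of a few months: about four for the end of data collection (31 December 2025 to 30 April 2026 at the longest), with the results date moving accordingly. The outcome, the visit rules, the sample size and the analysis model stay as they are.
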